## Abstract

**Background:**

Parkinson’s disease (PD) is associated with changes in gait and posture, which increases the rate of falls and injuries in this population. Tai Chi (TC) training enhances the movement capacity of patients with PD. However, the understanding of the effect of TC training on gait and postural stability in PD is lacking. This study aims to examine the effect of biomechanical-based TC training on dynamic postural stability and its relationship with walking performance.

**Methods/design:**

A single-blind, randomized control trial of 40 individuals with early-stage PD was conducted (Hoehn and Yahr stages 1 to 3). Patients with PD will be randomly assigned to either the TC or control group. The TC group will participate in a biomechanical-based TC training program that is formed based on the movement analysis of TC and will be practiced thrice a week for 12 weeks. The control group will be required to engage in at least 60 min of regular physical activity (PA) on their own for three times per week for 12 weeks. The primary and secondary outcomes will be assessed at baseline and at 6 and 12 weeks after commencing the study protocol. The primary outcome measures will include dynamic postural stability indicated by the center of mass and center of pressure separation distance and clearance distance of the heel and toe measured during fixed-obstacle crossing. The secondary measures are gait speed, cadence, step length during level surface walking (simple task), and fixed-obstacle crossing (challenging task). The Unified Parkinson’s Disease Rating Scale, single leg-stance test with eyes open and closed, and three cognitive scores (Stroop Test, Trail Making Test Part B, and the Wisconsin Card Sorting Test) were also employed.

**Discussion:**

This protocol could lead to the development of a biomechanics TC training program for the improvement of gait and postural stability among individuals with PD. The program could enhance the understanding of the effect of TC training on gait and postural stability and could help improve or preserve the postural stability, self-confidence, and active participation in social activities of the participants, thus enhancing their overall quality of life.

**Trial registration:**

ClinicalTrials.gov NCT04644367. Registered on 25 November 2020.

**Supplementary Information:**

The online version contains supplementary material available at 10.1186/s13063-023-07146-x.

## Administrative information

Note: the numbers in curly brackets in this protocol refer to SPIRIT checklist item numbers. The order of the items has been modified to group similar items (see http://www.equator-network.org/reporting-guidelines/spirit-2013-statement-defining-standard-protocol-items-for-clinical-trials/).

## Introduction

### Background and rationale {6a}

Parkinson’s disease (PD) is a growing concern in Canada, where approximately 100,000 people are living with PD; this number is expected to rise to 163,700 by 2031 [1]. The direct and indirect socioeconomic costs in Canada associated with this neurological condition are estimated to be more than $1.214B [2]. Postural instability and gait difficulties are common problems reported among people with PD [3, 4]. People with PD have difficulties with daily tasks such as walking caused by gait-related changes in step width and step length that can lead to reduced walking speeds. This “cautious gait” approach is similar to older adults who are at a high risk of falls [5, 6]. Falls and the loss of the ability to live independently are among the key concerns of people with PD. A 1-year follow-up study among 109 subjects with idiopathic PD diagnosed according to the brain bank criteria reported a fall occurrence of 68.3% [7].

Exercise intervention programs are being used in conjunction with drug therapy (such as levodopa, carbidopa) as standard of care to manage the symptoms related to PD [8, 9]. Tai Chi (TC) is a body-mind exercise that has been recommended by *Parkinson’s Canada* as one of the few exercise programs specific for those with PD [10]. TC training is suggested to help improve the awareness of whole-body movement and joint proprioception and increase muscle strength and endurance of the lower limb, thus strengthening the neuromuscular reaction of muscles in the lower extremities [11, 12]. For people with PD, TC training would help in challenging postural stability, particularly in the mediolateral (M-L) direction that is closely related to fall prevention. It will also strengthen the muscles at the hip involved in postural control. Regular TC practice and training would lead to improvements in gait and postural stability by encouraging weight shifting, control displacement of the COM over the base of support, and comfort with stepping in different directions.

### Objectives {7}

Several TC studies for PD have been published [13, 14]. However, details about how TC programs were formulated or how TC forms were selected are unknown. This missing information may affect the training effect because TC has many forms and has different styles. Moreover, the effect of TC training on dynamic postural stability and how it relates to walking performance and challenging walking, such as obstacle crossing, is unclear. This information gap can be difficult for people with PD, because dynamic postural stability is challenged. This study aims to examine the impact of a biomechanics-based TC program training on gait and postural stability, particularly on dynamic postural stability and how it relates to walking performance and obstacle crossing. Based on our previous studies [11, 15, 16], it is hypothesized that a biomechanics-based TC program training will help in improving gait and dynamic postural stability by increasing walking speed, stability in mediolateral (M-L) direction, and toe and heel clearance distance during obstacle crossing in the individuals with PD. This protocol could lead to the development of an innovative balance and gait training program tailored to individuals with early-stage PD.

### Trial design {8}

A single-blind randomized control trial will be conducted to compare the effects of a TC program with a physical activity (PA) routine (Fig. 1). The study will be conducted for 12 weeks (3 months), and this period will include a 12-week intervention period with primary and secondary outcomes measured at baseline and at 6 and 12 weeks.

**Fig. 1 Fig1:**
[figure not shown]
Flow diagram of TC study with design and illustration of experimental and control groups’ allocation

## Methods: participants, interventions, and outcomes

### Study setting {9}

University of Ottawa’s Human Movement Biomechanics Laboratory will serve as the primary site for the study. TC interventions will be offered at community centers in Ottawa, Canada. The PA routine can be performed inside or outside the home environment.

### Eligibility criteria {10}

Participants will be included in the study if they meet the following criteria:Have been diagnosed with PD and demonstrate a disease severity ranging from 1 to 3 on the Hoehn and Yahr (H&Y) scaleHave no fluctuations in motor symptoms as reported by the motor section of the Unified Parkinson’s Disease Rating Scale (UPDRS-III)Have stable PD (such as levodopa or carbidopa) and doctor-prescribed medication use, that is, fluctuation did not occur at the time of medication intakeCan stand and walk independentlyAvailable thrice a week over a period of 12 weeksBe able to engage in PA for at least 60 min on their own, thrice per week, without prior experience practicing TC regularly

Participants will be excluded from the study if any of the following conditions are reported:Enrolled into any other behavioral or pharmacological studiesHave a Montreal Cognitive Assessment (MoCA) score of < 26/27 (that indicates some mild cognitive impairment (MCI)) [17]Have had a serious medical condition or uncontrolled hypertension (equal or greater than a systolic 180 or diastolic 110 reading)Have any debilitating conditions that could prevent them from performing any PA for a minimum of 60 minHave practiced or have experience of practicing TC in an organized class or program within the last 5 years at the start of participation in the study

### Who will take informed consent? {26a}

The primary investigator will obtain informed consent from the potential trial participants.

### Additional consent provisions for collection and use of participant data and biological specimens {26b}

No secondary participant information or data will be collected, nor any biological specimens will be collected.

### Interventions

#### Explanation for the choice of comparators {6b}

The two comparators are the TC intervention and PA group (control group). The two comparators were chosen to understand the effect of 12-week biomechanical-based TC training on the gait and posture of people with PD compared with those who will maintain their regular PA. An active PA (control) group was chosen for avoiding an unfair comparison to participants who are sedentary or who are inactive.

#### Intervention description {11a}

## TC program development

The biomechanical-based TC training program has been developed based on research with an experienced TC master, our previous work, and by biomechanical analysis of TC movement. Seven TC movements were chosen based on the following considerations:Easy to learn.Feasible to practice.Can be practiced either individually or in groups.Space requirement is minimal (e.g., practicing inside the home, living room, or yard).The seven selected TC movements and the three static and four dynamic forms are listed in Table 1. A static TC movement was defined as the movement in which the center of mass (COM) was maintained within the limits of the body’s base of support (BOS), whereas a dynamic TC movement was defined as the movement, in which the body’s COM was outside the limits of the body’s BOS. Figure 2 illustrates three dynamic TC movements from the seven TC movements. These TC movements are typical TC movements and are present in all classic TC styles, such as Wu, Yang, and Chen styles [18]. The biomechanical analysis of the seven selected TC movements in terms of their kinematics, kinetics, and muscle activities demonstrates their unique features compared with walking. These movements require increased foot clearance, step length, and movement in the backward, sideway, 45° angle, and forward directions [15, 19]. Regular performance of these movements would result in special training to postural control, particularly in the adductor and tensor fasciae latae muscles that are responsible for maintaining M-L postural stability and assisting in preventing falls [15, 16]. TC training can help in challenging M-L stability through shifting of the body’s COM, using the full range of motion of joints, and increasing step width [15, 16]. Electromyography activity while performing the seven TC forms has revealed a higher activation of the hip adductor muscles compared with walking, suggesting that good muscle training prevents lateral falls [18].

**Table 1 Tab1:** 7-form TC program for people with PD

TC form	Characteristics
Form 1: Starting form	Standing (arms): arms from down to up
Form 2: Hero lift the sky	Standing (arms): push up to down
Form 3: Standing, push hand back	Standing (arms): neutral to back
Form 4: Wave-hand-like-cloud	Sideway stepping: left and right
Form 5: Brush knee twist step	Forward diagonal stepping: left and right
Form 6: Repulse monkey	Backward diagonal stepping: left and right
Form 7: Lateral forward step	Lateral diagonal stepping: left and right

**Fig. 2 Fig2:**
[figure not shown]
Illustration of four dynamic forms from the proposed 7-form TC program

## TC training group

For the TC group, the first 2 weeks of the program will require the participants to work on some light breathing and simple upper-limb forms. The basic TC forms will be introduced with a focus on becoming comfortable with the flow and rhythm of the movements. Each session will run for 60 min and will be supervised by a TC instructor in a community center. The training will be gradual and range from low to moderate intensity. Participants will warm up for 5–10 min, perform core activities for 40 min, and cool down for 5 min. Three sessions will be offered weekly for 12 weeks; the participants will be asked to attend at least two sessions per week. The third to sixth week of the program will focus on incorporating the upper and lower limb into the routine. These classes will focus on practicing the seven TC forms sequentially. The six remaining weeks of the program will focus on repetitions and performance mastery of the basic seven-form routine. The participants will be allowed to practice TC at home. Any TC that the participant performs in their home or on their own time will be recorded by themselves by using a monitoring form that will be distributed to them and collected weekly. The TC instructor will be present at each of the session to monitor the participants’ progress and to ensure that the movements are being performed correctly.

## Physical activity group

The PA group will track their level of PA over 12 weeks. During this period, the participants will be required to engage in at least 60 min of regular PA on their own for three times per week. Regular PA may include walking, cleaning, performing chores inside the home, and/or climbing the stairs. No restriction will be made to limit other forms of PA. Individuals in the PA group will be permitted to engage in organized sports and instructor-led class such as boxing and dance to ensure that the participant recruitment process is feasible. An active control group was used for comparisons between the groups who will or will not receive formal TC training and to reflect the daily lifestyle and activities of a typical individual with PD from the community. Similar to the TC group, the participants in this group will be asked to complete an activity log form for monitoring, and this form will be collected weekly to monitor their regular PA levels.

### Criteria for discontinuing or modifying allocated interventions {11b}

At any point during the study, either during the intervention period or laboratory testing sessions, the participants will be free to refuse to participate. If he or she chooses to participate, the participant may withdraw from the study at any time for any reason.

### Strategies for improved adherence to interventions {11c}

For the group receiving the TC intervention, three class sessions will be offered weekly for 12 weeks. The participants will be asked to attend three sessions per week. These classes will be monitored by the PI and TC master. This set-up will ensure that the classes are offered at a flexible time for the participant that match their availability and schedules. The participants of the PA group will be asked to maintain regular PA levels and complete an activity log form for monitoring. This form will be collected weekly to monitor their regular PA levels to ensure that they will be motivated and consistent in their PA engagement and performance.

### Relevant concomitant care permitted or prohibited during the trial {11d}

No concomitant care and intervention requirements are either permitted or prohibited during the trial. The participants will be asked to maintain their medication dosage and any mandatory medical care or aid that they are receiving during the intervention period. To encourage engagement and enrollment into the study, we allowed the TC and PA groups to engage in forms of exercise and PA, and no restrictions will be made, because this set-up will not affect the outcome or results of the study.

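### No rule asks controls to refrain from Tai Chi during the 12 weeks, and the stated reason for leaving exercise unrestricted is unsupported

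*Protocol article*

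**What the plan says.** All references are to the protocol article.

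- **Concomitant care {11d}** opens with "No concomitant care and intervention requirements are either permitted or prohibited during the trial". It then lets both groups exercise as they wish, to help enrolment, and gives the reason: "no restrictions will be made, because this set-up will not affect the outcome or results of the study".
- **Physical activity group** (under {11a}) says of controls "No restriction will be made to limit other forms of PA". They are "permitted to engage in organized sports and instructor-led class such as boxing and dance", again for feasibility of recruitment. The same section gives the purpose of the arm: "An active control group was used for comparisons between the groups who will or will not receive formal TC training". A weekly activity log is kept, and "this form will be collected weekly to monitor their regular PA levels".
- **Eligibility {10}** admits only people without regular Tai Chi experience and excludes organised Tai Chi in the 5 years before entry. Both conditions look back from enrolment.
- **Choice of comparators {6b}** and **Strategies for improved adherence {11c}** describe controls as keeping up their usual activity.
- **Statistical methods {20a}** analyses participants in the group to which they were randomised, whatever they actually did.

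**The concern.** The contrast the trial needs is Tai Chi against no Tai Chi. The article protects it before entry but has no instruction that protects it during the 12 weeks in which the effect is measured. Analysis by allocated group is the right choice, but it means that any control who takes up Tai Chi and benefits moves the control mean towards the Tai Chi mean. The sample size section allows for dropout and nothing else.

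The background also makes some uptake plausible. Tai Chi is described as "recommended by *Parkinson’s Canada* as one of the few exercise programs specific for those with PD", and support groups associated with that organisation are one of the three recruitment sources in Recruitment {15}.

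Separately, the reason given for having no restriction is a factual claim about gait and balance outcomes that the rest of the article does not bear out.

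**Working it through.** **1. The no-effect claim set beside the rest of the article**

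- The Discussion reports that 12 weeks of treadmill training improved walking distance and that resistance training can raise strength. It calls such programmes limited in effectiveness, but limited is not the same as no effect on gait or posture.
- The Discussion likens Tai Chi to rhythmic exercise such as tango and ballroom dance. Dance is one of the two classes named as open to controls.
- The Discussion says earlier Tai Chi programmes benefited posture, gait and mobility.
- Additional analyses {20b} says efforts were made so that only the effects of Tai Chi training are examined. That is hard to square with unrestricted exercise in both arms.

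The claim in {11d} is unsupported whatever the number of controls who take up Tai Chi.

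**2. Reproducing the stated power**

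Inputs from Sample size {14} and Sequence generation {16a}: 40 participants, 1:1 (20 per arm), alpha 5%, difference 1.13, power 93%. Two assumptions are needed: a two-sided test, and 1.13 read as a standardised difference, since no unit or standard deviation is given.

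Two-sample t test with n per arm: noncentrality λ = d × √(n/2), degrees of freedom 2n − 2.

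With d = 1.13 and n = 20, λ = 1.13 × √10 = 3.57 on 38 degrees of freedom, and power is 93.6%. By the normal approximation 93% power needs 19 per arm, and 38 / 0.95 = 40. A one-sided test gives about 97%. The stated 93% is reproduced and is not in question.

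**3. Effect of uptake in the control arm**

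Let c be the share of controls who take up Tai Chi and f the fraction of the programme's effect that each gains. The expected difference becomes d = 1.13 × (1 − c × f). The documents give neither c nor f. The table takes f = 1, the worst case. The last column also allows for the extra spread in a control arm that mixes two kinds of participant, using an average SD of √{[2 + c(1 − c) × 1.13²] / 2}.

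| Assumed uptake c | Controls of 20 | Difference | Power, SD unchanged | Power, mixed control arm |
|---|---|---|---|---|
| 0% | 0 | 1.13 | 93.6% | 93.6% |
| 5% | 1 | 1.07 | 91.1% | 90.3% |
| 10% | 2 | 1.02 | 88.0% | 86.2% |
| 20% | 4 | 0.90 | 79.6% | 75.6% |
| 30% | 6 | 0.79 | 68.4% | 62.9% |

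If each such control gained only half the effect (f = 0.5), 20% uptake would give 1.13 × (1 − 0.10) = 1.02, and power of 88.0% with the SD unchanged.

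**The case against.** The strongest reply is that the control condition is described elsewhere. Sections {6b} and {11c} have controls keeping up their usual activity. Eligibility means that nobody's usual activity at entry should include organised Tai Chi, and the named classes are boxing and dance. On that reading a new Tai Chi class already departs from the control condition. Unrestricted activity is also a deliberate choice, made for recruitment and to reflect typical daily life with Parkinson's disease.

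Much of this stands. A reader might infer that the article expressly allows controls to do Tai Chi. It does not: the matter is left unaddressed, and "comparisons between the groups who will or will not receive formal TC training" shows the intent. But a description of intent is not an instruction, and the no-restriction wording in two sections pulls the other way.

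Three further inferences are tempting and not supported:

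- **That uptake of 10–30% is to be expected.** No rate is given. Everyone eligible has gone 5 years without organised Tai Chi despite the recommendation, which argues for low uptake. Eligibility {10} and Objectives {7} together also weaken the full-effect assumption: entrants are new to Tai Chi, and the article says forms and styles differ in ways that may affect the training effect.
- **That controls know they were denied the classes and will seek them out.** No section says so, and Participants to be blinded {17a} defers full disclosure of the aims to the end of the intervention period.
- **That a null result could not be interpreted.** The weekly logs could show Tai Chi use, and dilution of this kind pulls towards no effect; it does not create a false positive.

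**Conclusion.** The point holds in a limited form. Two sections leave exercise unrestricted and none asks controls to refrain from Tai Chi during the trial, while the purpose of the control arm, the eligibility criteria and the description of usual activity all presuppose that they will. The sections need to be reconciled. The claim that unrestricted exercise cannot affect the results should go, because the article's own Discussion and {20b} contradict it.

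The size is conditional. If no control takes up Tai Chi, nothing is lost. Under full-effect uptake of 5% to 30%, power falls from 93.6% to between 91.1% and 68.4%. This rests on a two-sided test, 1.13 as a standardised difference, 20 per arm and an unchanged SD. Partial uptake or effect loses less; the extra spread of a mixed control arm loses a few points more. The figures illustrate sensitivity and do not predict what will happen.

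**What to change.** 1. Reconcile {10}, {6b}, the Physical activity group section, {11c} and {11d} so that they say the same thing: controls are asked not to start Tai Chi before their week-12 assessment, and all other activity stays free. This keeps the pragmatic comparator.
2. Add a Tai Chi line to the weekly activity log already collected from controls. The Tai Chi group's form is described as recording own-time Tai Chi, so it may need a line for other exercise to make the arms comparable.
3. Report Tai Chi and other structured exercise by arm. Keep anyone who takes up Tai Chi in follow-up and in the allocated group.
4. Delete the statement in {11d} that the lack of restriction will not affect the results. The recruitment rationale can stand alone.

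**Cost:** one sentence of instruction and one line on a form. Some recruits may dislike deferring Tai Chi. The instruction may also hint at the aim that {17a} discloses only at the end; listing Tai Chi neutrally among other activities on the log lessens this.

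Trial status gives December 2021 as the planned completion. If follow-up is already over, item 1 no longer applies, but existing logs can be searched for Tai Chi, the counts reported by arm, and the claim withdrawn.
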